### Criteria for modifying and discontinuing

#### Criteria for discontinuing

Patients are instructed to stop exercising if they experience a *strong flare up* or a *strong aggravation* of knee-related symptoms (e.g., pain and swelling), i.e., knee-related symptoms that are intolerable for the patient. Correspondingly, patients are encouraged to complete the exercise if they experience minor and moderate knee-related symptoms [32]. Should the patients experience intolerable symptoms (stopping with exercise); they are provided with a telephone number to a physiotherapist (the trial manager) and are encouraged to call. The trial manager fills out a standardized form at these calls.

#### Criteria for modifying

Should the patients experience strong knee-related symptoms, they are instructed to lessen the resistance in the elastic exercise band (shortening the distance between the endpoints of the elastic exercise band, i.e., moving the chair closer to the door (Fig. 3)). Importantly though is that this reduced resistance in the elastic exercise band does not comprise the exercise resistance corresponding to 12 RM, (i.e., too little resistance in the elastic exercise band). This is explained to the patients at the exercise instruction session and mentioned in the brochure handed to the patients along with the elastic exercise band (Additional file 3).

### Participant compliance, retention and concomitant care

At the baseline outcome assessment and at the exercise instruction session the patients are encouraged to complete the full intervention and the patients are handed an information brochure about both how to conduct the exercise, with encouragement to complete the intervention and with information on how to handle kinesiophobia (Additional file 3). Further, the patients have two exercise quality check-up visits (booster visits): one at 4 weeks and one at 8 weeks, with the physiotherapist in the municipality setting. These booster visits also serve as promoters for exercise adherence. The patients should continue their lives without changing any concomitant care or interventions, except extra exercise of the quadriceps muscle. For pain relief the patients are allowed use of non-steroidal anti-inflammatory drugs (NSAIDs) and other pain-reducing products (cf. the Danish National Guidelines for knee OA [3]), as they would normally do, not needing a physician’s prescription.

### Outcomes

The trial is designed with four pre-determined outcome assessments; at baseline (week 0) (t_0_), after 12 weeks of home-based exercise (2–8 days after the final exercise session), corresponding to the endpoint before surgery (t_1_), at hospital discharge 1–8 days after surgery (t_2_) (provided surgery is performed) and finally, 3 months after surgery (t_3_) (Fig. 2) (provided surgery is performed). The primary endpoint is after the intervention period (t_1_). Secondary endpoints of interest are just before hospital discharge 1–8 days after surgery (t_2_) and 3 months after surgery (t_3_).

#### Primary outcome

Change in isometric knee-extensor strength from baseline (week 0) to after the intervention period (> 12 weeks). Knee-extensor strength is chosen as the primary outcome for the following reasons. Firstly, it is an outcome closely related to the exposure (strength training), which we consider important in a dose-response trial, because other health effects are likely mediated via increased knee-extensor strength. Secondly, knee-extensor strength is associated with the development and progression of knee OA and knee pain and function [9, 10], and as such, we also consider the outcome, a surrogate measure for the development and progression of knee OA, knee pain and function.

#### Secondary outcomes

Change in performance-based function (walking distance in 6 min and climbing of stairs), current knee pain and during the last week (numerical rating scale), self-reported disability (Knee Osteoarthritis Outcome Score and Oxford Knee Score) as recommended by Osteoarthritis Research Society International [33, 34], need for surgery and exercise adherence (sessions, sets, reps, TUT).

#### Other outcomes

Registration of adverse events (adverse event, number of adverse events in each group (surgery/no surgery).

At outcome assessment endpoint t_2_ (after surgery at hospital discharge) only the outcomes *isometric knee-extensor strength, 6-Minute Walking Test (6MWT), SCT* and *current knee pain* are assessed. The *KOOS* and *OKS* questionnaires as well as *knee pain during the last week* are omitted at this endpoint as they are not validated to assess acute post-operative conditions, and use too long a recall period.

### Elaborated description of outcome measures

#### Primary outcome

##### Isometric knee-extensor strength

The measurement will be assessed using a computerized strength chair (Good Strength Chair, Metitur Oy, Jyvaskyla, Finland). This is a valid (0.78–0.92) and reliable (inter-trial 0.98–1.00 (standard error of measurement (SEM) < 10%), inter-evaluator 0.92–0.99 (SEM 8.34–9.92%)) knee-extensor strength measure in the TKA population [35].

Prior to outcome assessment, the patients will be informed about the procedure. The measurement consists of five maximal isometric knee-extensor contractions at 60° knee flexion separated by a 60-s pauses. The highest obtained value will be used for analysis. The patients are instructed to extend their knee as forcefully as possible with a gradual increase in force over a 5-s period. There will be strong and standardized verbal encouragement during each contraction. Knee-extensor strength will subsequently be expressed as the maximal voluntary torque per kilogram body mass (Nm/kg) using the external lever arm and body mass of each patient. Results will be presented, firstly, as absolute changes (Nm/kg) and, secondly, as relative changes (%) from baseline.

#### Secondary outcomes

##### 6-Minute Walking Test for distance (6MWT)

The 6MWT measures the maximal distance a patient is able to walk in 6 min between two cones placed 29 m apart from each other. The measurement has previously been found to be reliable (intraclass correlation coefficient (ICC)_2,1_ 0.97, SEM 13.0 m) [36] and responsive [37] in the TKA population.

The patients are instructed to walk as long a distance as they can in six minutes. They will be encouraged to walk as fast as possible but are not allowed to jog or run. The patients are allowed to rest standing or leaning against a wall during the six minutes but the time will be running. Walking aids are allowed if needed. At each minute the patients will be informed of the time.

##### Stair Climb Test (SCT)

The SCT measures the time (seconds) it takes to ascend and descend an 11-step flight of stairs with 16-cm step height. The stair has a handrail on both sides. The SCT has been found to be reliable in the TKA population (inter-tester ICC_2,1_ 0.94–0.96, SEM 1.14 s, minimal detectable change (MDC)_90_ 2.6 s) [38]. The patients are instructed to ascend and descend an 11-step flight of stairs as fast as possible, but in a safe manner. Use of hand rail and walking aid is permitted. The patients are allowed to rest during the measurement but the time keeps running.

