Patients with knee OA are characterized by decreased knee-extensor strength and this decrease in knee-extensor strength is associated with limitation of activities of daily living, independent of knee pain [7, 8]. Correspondingly, knee-extensor muscle weakness is found to be associated with increased risk of developing knee OA, progression of knee OA, symptoms of knee pain and decline in function [9, 10]. Clinically, patients diagnosed with end-stage knee OA who are awaiting TKA to reduce pain and disability are reported to have 35% reduced knee-extensor strength compared to healthy, age-matched persons [7]. Shortly after TKA, patients lose an additional 80% of their pre-operative knee-extensor strength [11]. This massive loss in knee-extensor strength severely limits functional performance and may delay hospital discharge in the large number of patients undergoing TKA every year [12]. One of the latest systematic reviews on the efficacy of exercise to reduce pain and disability in patients with knee OA showed that isolated knee-extensor strength exercise was more effective in reducing pain and disability if not combined with other forms of exercises (e.g., other muscle groups or cardiovascular training) [13]. In line with this, the 2014 international guidelines for non-surgical management of knee OA include strength exercise of the knee-extensor muscles [14].

Two recent randomized controlled trials have indicated that high-volume, pre-operative strength exercise may enhance pre- and post-operative knee-extensor strength as well as functional performance in patients undergoing TKA [15, 16]. Hence, there are indications that the applied pre-operative exercise dose seems related to pre- and post-operative efficacy, making a dose-response trial of pre-operative exercise particularly relevant.

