### Trial design

The trial is named the *QUADX-1 trial*. It uses a three-arm, parallel-group, randomized trial design with three intervention groups (exercise dosages) and no control group. No control group is included as the primary purpose of the trial is to investigate the dose-response relationship of the investigated knee-extensor strength exercise dosages. Based on the sample size estimation outlined below, 140 patients will be randomized (1:1:1) to one of three exercise dosages for 12 weeks. Outcomes will be assessed blinded at baseline before the start of the exercise (t_0_), after the exercise intervention, which is before possible surgery (t_1_, primary endpoint), at hospital discharge 1–8 days after surgery (if performed) (t_2_) and, finally, at 3 months after surgery (if performed) (t_3_). A flow chart of the trial is provided below (Fig. 1).

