### Missing data

All analyses will follow the intention-to-treat (ITT) principle with a clear registration and reporting of the drop-out rate. All patients will be analyzed as randomized. To create a full analysis dataset for the intention-to-treat analyses, missing data will be imputed using multiple imputations.

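### An operated patient who attends t2 but cannot climb the stairs has no SCT time, and the blanket imputation rule would treat that poor result as ordinary missing data

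*Protocol article*

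**What the plan says.** The Stair Climb Test section gives the outcome a single definition: "The SCT measures the time (seconds) it takes to ascend and descend an 11-step flight of stairs with 16-cm step height". Two allowances make completion easier: "Use of hand rail and walking aid is permitted", and "The patients are allowed to rest during the measurement but the time keeps running". The section states neither a maximum time nor a value for a patient who does not finish.

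The Trial design and Outcomes sections place t2 at hospital discharge, 1–8 days after surgery. The Other outcomes section drops KOOS, OKS and last-week pain at that visit and keeps the SCT: "only the outcomes *isometric knee-extensor strength, 6-Minute Walking Test (6MWT), SCT* and *current knee pain* are assessed". Table 3, row 6, analyses change in SCT time, including t0–t2, as a continuous variable by ANOVA. Its footnote moves to Kruskal-Wallis if data are not normally distributed and does not mention inability.

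The Missing data section covers all analyses with one rule: "To create a full analysis dataset for the intention-to-treat analyses, missing data will be imputed using multiple imputations". It makes no distinction by reason for missingness and does not describe the imputation model.

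The Background explains why inability is foreseeable at t2: "Shortly after TKA, patients lose an additional 80% of their pre-operative knee-extensor strength". It adds that this loss severely restricts function.

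**The concern.** A stair time exists only for patients who complete the stairs. Someone who attends t2 and cannot do so has shown a poor functional result, but the data set holds a blank. Under the stated rule that blank is imputed.

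Multiple imputation in its usual form assumes that, given the variables in the model, patients without a value resemble those with one. Here the value is absent because the patient is too slow or too weak to produce it, so the imputed time tends to be too fast.

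At stake is the t0–t2 SCT contrast between dosage groups. The SCT is one of only two performance-based function measures kept at t2, and the Discussion says the results will indicate whether any effect on strength and function is sustained after surgery. If one dosage leaves more patients unable to climb, part of that difference is replaced by imputed times.

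**Working it through.** **Plan's own figure.** The protocol gives no SCT mean, SD, target difference or inability rate, so there is no SCT figure to reproduce. Its only design calculation, 42 per group for the primary outcome, reproduces closely (79.5% power by one-way ANOVA with SD 0.22, extremes 0.15 apart and the third group midway). It does not bear on this point. All inputs below are assumptions.

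**1. Size and direction of the error.** Let a2 and a4 be the mean times of able patients in groups 2 and 4, p2 and p4 the proportions unable, and U a time assigned to inability. If unable patients are imputed at their own group's able mean, the contrast is

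a2 − a4.

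If inability is scored at U, it is

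[(1 − p2)·a2 + p2·U] − [(1 − p4)·a4 + p4·U].

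Take a2 = 48 s, a4 = 42 s, U = 120 s. The imputed contrast is always 48 − 42 = 6 s.

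- 30% against 15% unable: (33.6 + 36) − (35.7 + 18) = 15.9 s. Imputation understates the difference.
- 20% against 20%: (38.4 + 24) − (33.6 + 24) = 4.8 s. Imputation gives slightly more.
- 15% against 30%: (40.8 + 18) − (29.4 + 36) = −6.6 s. Imputation gives the opposite sign.

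**2. Inability as the slow tail, with imputation from covariates.** Assumptions: median t2 time 45 s in the slower arm, SD 0.5 on the log scale, correlation 0.6 with baseline, and a patient is unable if the underlying time exceeds 75 s. The faster arm is shifted by 0.1, 0.2 or 0.3 log units. The second model adds another t2 measure, equal to the log time plus noise with SD 0.3. Large-sample results (percentages from unrounded values):

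| Unable, slower / faster arm | True contrast | Imputed from arm and baseline | With another t2 measure |
|---|---|---|---|
| 15% / 11% | 4.9 s | 2.9 s (58%) | 77% of true |
| 15% / 8% | 9.3 s | 5.6 s (61%) | 79% of true |
| 15% / 5% | 13.3 s | 8.5 s (64%) | 81% of true |

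In the slower arm the unable had a true mean of 100 s. They were imputed at 54 s from arm and baseline, or 77 s with the other t2 measure; able patients averaged 42 s.

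Three boundary cases:

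- No dosage effect (15% unable in both arms): both contrasts are about 0.
- Inability unrelated to stair ability: the imputed contrast is 1.00–1.01 of true.
- Few unable: raising the limit to 110 s (about 4% against 1–2% unable) retains 82–86%, or 92–93% with the other t2 measure. Raising it to 145 s (1% against under 1%) retains 92–94%, or 97%.

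**3. Power.** Assumptions: two arms of 47 (140/3, an upper bound because not all patients are operated), log-time SD 0.4, true difference 0.25 log units, baseline correlation 0.4, and a common cut-off for inability. The worse arm's rate is 1 − Φ[Φ⁻¹(1 − p) − 0.25/0.4], where p is the better arm's rate. Regression on arm and baseline among completers stands in for imputation. The comparator is a rank test with the unable placed last.

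| Unable, better / worse arm | Estimate (true 0.25) | Power, completers' regression | Power, worst rank |
|---|---|---|---|
| 1% / 4% | 0.226 | 87% | 85% |
| 2% / 8% | 0.213 | 84% | 84% |
| 5% / 15% | 0.188 | 76% | 83% |
| 10% / 26% | 0.165 | 67% | 82% |
| 20% / 41% | 0.133 | 49% | 82% |

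Powers move by two or three points between repeat runs. Worst ranking gains nothing at 1–2% unable and gains clearly from about 5%.

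**The case against.** The strongest objection is that scoring of an uncompleted performance test usually sits in a test manual, case report form or analysis plan. The Recruitment section mentions a separate outcome-assessment protocol, piloted in seven patients, and the Data management section a standardized case report form; neither is shown. The Missing data section also does not say that inability counts as missing. So the lack of a score for inability is not in itself an error. What remains is that the article does state a missing-data rule, for all analyses and without exception, and that rule suits this outcome badly. If a scoring rule exists elsewhere, the two need reconciling.

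Inability may also be rare. The 80% figure is a loss of strength, not a rate of stair failure. Assessment is tied to discharge, which weakness may delay. With a handrail, aids and rests allowed and no time limit, a very slow patient still has a time. All this stands, and it is why no size can be claimed.

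A reader might infer that the rule is certain to shrink the dosage contrast, or that unable patients simply receive the times of those who could climb. The documents support neither. Shrinkage needs a dosage effect with inability following it; other patterns leave the contrast unchanged, enlarge it or reverse it. Imputation draws on each patient's covariates, the model is not specified, and strength, 6MWT and current pain at t2 could all enter it. That reduces the error in the example without removing it.

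Finally, ranking as worst a patient kept off the stairs for reasons unrelated to function would add its own error. The fix has to separate the two groups.

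**Conclusion.** The point holds in limited form. Applied as written, the imputation rule turns a failed stair test at t2 into an ordinary missing value and fills it with a time that is too fast. This can shrink or distort the t0–t2 SCT contrast when inability differs between dosage groups.

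The size is unknown. In the illustrations the retained share of the contrast runs from 58% (about 15% unable in the slower arm, imputation from arm and baseline only) to 97% (about 1% unable, richer model). These figures rest on assumed times, spreads, correlations and inability thresholds, and on inability reflecting poor stair function. If very few patients are unable the effect is negligible, and with no dosage effect and equal inability there is no bias in the contrast.

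The reach is one secondary outcome at one secondary endpoint. The primary analysis of knee-extensor strength at t1 is unaffected.

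**What to change.** In the Stair Climb Test section, add two codes for operated patients at t2: attempted or assessed but unable because of function, and not tested for other reasons. The blinded assessor should record the code and reason at the visit. Report the number unable in each dosage group.

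In Table 3, row 6, analyse SCT at t2 with patients unable because of function ranked worst, using the Kruskal-Wallis test the plan already names. In the Missing data section, state that for SCT at t2 multiple imputation applies only to operated patients not tested for other reasons.

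The cost is a sentence in each section, one field on the case report form and a rank test for one secondary outcome. The t2 contrast is then no longer a mean difference in seconds, though the completers' mean can still be shown descriptively. If almost nobody is unable, the rank test brings no gain in power, but the counts per group will show that.

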##### Knee Osteoarthritis Outcome Score (KOOS)

The KOOS is a 42-item questionnaire regarding knee function. The questionnaire is comprised of five subscales (symptoms (7), pain (9), function, daily living (17), function, sports and recreational activities (5) and quality of life (4). Each question has standardized answer options with five options at each question (Likert scale, 0–4). After normalization of the answers each subscale scores from 0–100 (100 indicating no symptoms). The KOOS questionnaire is found to be reliable in all subscales (pain ICC 0.8–0.97, SEM 7.2–10.2; symptoms ICC 0.74–0.94, SEM 7.2–9.0; daily living ICC 0.84–0.94, SEM 5.2–11.7; sports ICC 0.65–0.92, SEM 9–24.6; quality of life ICC 0.6–0.91, SEM 7.4–10.8) [39]. The KOOS questionnaire is also found be to reliable in the TKA population [40].

##### Oxford Knee Score (OKS)

The OKS is a 12-item questionnaire regarding knee-related function and pain in patients with knee OA. Each question has five answer options (Likert scale, 0–4). The OKS demonstrates good test-retest reliability for both the summary scale (ICC 0.93, MDC_90_ + 6), pain (ICC 0.91, MDC_90_ ± 16) and function (ICC 0.92, MDC_90_ ± 15) component subscales [41].

##### Knee pain

Individual knee pain is assessed with the Numeric Rating Scale (NRS). This is an 11-point subjective pain scale ranging from 0–10 (0 indicating no pain). In this trial, the patients will be asked about their knee pain related to two endpoints: (1) knee pain right now and (2) during the last week. The question is asked in the following manner “on a scale from 0 to 10 where 0 indicates no pain and 10 indicates worst imaginable pain, how much knee pain do you have (1) right now and (2) how much knee pain have you had in the last week (index knee)?” The patients are asked while seated in a chair with 70–90° of knee flexion (standardized). The NRS is found to have the strongest face validity compared to other pain measurement scales (Visual Analog Scale and Verbal Descriptor Scale) in surgical patients after surgery as well as high construct and criterion validity [42]. The NRS is also found to be reliable both before (ICC 0.82) and in the first 1–6 days following surgery (ICC 0.673–0.783) [43]. A minimal clinically important difference in pain relief post orthopedic surgery has previously been suggested to be 35% [44].

##### Surgical status – Need for surgery?

At the second outcome assessment (after the 12-week exercise period (t_1_)) the patients are asked by the outcome assessor “*based on your knee symptoms in the last week would you say that you need knee surgery?*” The outcome assessor is a physiotherapist with insight to the knee OA condition. The answer will be categorized into one of three options: (1) “*yes*” *I believe I need surgery*, (2) *I do not know* or (3) “*no*” *I do not believe I need surgery*.

##### Exercise adherence

A large challenge regarding home-based exercise is that adherence to home-based exercise is reported to be poor [45–48], suggesting low effect of the exercise interventions. To take into account the possibility of non-adherence to the intervention (which could distort the possible conclusion that the intervention did not work), we will objectively quantify exercise adherence. Adherence to the home-based, single knee-extensor strength exercise will be assessed using a sensor (BandCizer technology) attached to the elastic exercise band used for the knee-extensor strength exercise. The sensor stores data on date, time, number of sets, repetitions, tonnage (kg × repetitions) and TUT. This elastic exercise band sensor technology has been reported to be valid [49] and reliable (ICC > 0.99) [50] for quantification of total repetition, single repetition and contraction specific TUT of an unsupervised exercise intervention.

In the present trial, patients are defined as adherent to the exercise intervention if > 75% of the prescribed exercise sessions are completed. Correspondingly, 1.5 sessions/week must be completed in group 2, three sessions/week in group 4 and 4.5 sessions/week in group 6. After the 12-week exercise period, the patients who undergo surgery are encouraged to continue exercising (same dosage) until the day of surgery. The exercise adherence during this period will also be quantified by use of the sensor. Patients deciding not to undergo surgery following the 12 weeks of exercise are encouraged to keep exercising, but exercise adherence will not be quantified. Figure 4 shows an example of objectively quantified exercise adherence via the sensor attached to the elastic exercise band. The example shows a knee-extensor strength exercise session composed of three sets with 12 repetitions in each set resulting in 36 repetitions in total for the exercise session. Number of repetitions, total TUT, mean TUT for the 36 repetition and the corresponding standard deviation can be extracted. This is also possible for single exercise sets (Fig. 5).

